|  | 6b | We examine the impact of new documentation media. Therefore, we compare a group of patients who report the occurred adverse events via the NEMO smartphone app and patients using standard reporting procedure. |
| Objectives | 7 | Patient acceptance of a new means of communication, Reduction of side effects by at least 1 degree according to CTCAE at study start. |

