| Trial design | 8 | This study will be implemented in two parts. The first part should evaluate the feasibility and acceptance of a smartphone-based adverse reaction documentation. It will be followed by a second part. which will compare the impact of smartphone reported adverse events regarding applied therapy doses to those of patient with standard care. For the detection of occurred adverse events at an early stage, the participants will answer a standardized questionnaire (Table 1 and 2) via the NEMO app every day. Depending on the underlying therapy scheme, the NEMO questionnaire can be selected for chemotherapy (Table 1) or combined immunotherapy (Table 2), targeted therapy, and chemotherapy. NEMO allows for switching the therapeutic settings in case the therapeutic scheme changes. During therapy sessions, the documented data is transmitted securely via QR-codes to the treating physician and used for future therapy settings. To assess the. feasibility, 30 patients will be divided non-randomly into three age groups (< 55 years, 55-75 years, >75 years) of 10 patients each. These people will be followed over six months. Participants will answer the respective NEMO questionnaire about adverse events on a daily basis over these six months. After six months, they will answer a questionnaire about user-friendliness and feasibility (Table 3). Evaluation of these questionnaires allows for studying the different patients' characters and their potential benefit of using NEMO. The answered questionnaires could also give insights to identify barriers to answering the questions. The results of this evaluation enable us to amend the criteria for recruiting patients of the second part, such as their age and improving the application for the second part of the study. To assess the reduction of adverse events, 36 participants will be randomly assigned a group of 18 persons (smartphone user and standard care). Again, smartphone users will answer their respective NEMO questionnaires every day about occurred adverse events for six months. The transfer of their reported data takes place every second month in parallel with the reevaluation of tumor therapy. Participants of the standard care group will report their occurred adverse events and duration only during their personal appointments. What the patient remembers and reports depends on each participant and is very individual. Based on these reported adverse events, physicians will delineate a CTCAE scoring. Physicians will additionally fill out an electronic case report form containing tumor stage and information about therapeutic substances and doses. Moreover, patients of both study arms will answer a questionnaire about life quality which is based on the European Organization for Research and Treatment of Cancer (EORTC) questionnaire at enrolment and once at the end of the study to investigate whether NEMO can improve the quality of life. |

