| Methods: Participants, interventions, and outcomes | | |
| Study setting | 9 | Study will be conducted at the University Hospital Ulm |
| Eligibility criteria | 10 | Inclusion Criteria:   - infusional combination therapy with at least two chemotherapy substances with or without further targeted therapies - combination of at least two immune-checkpoint inhibitors - able to read and understand German   Exclusion Criteria:  Participants who meet any of the following criteria will be excluded:   - severe neurological disorders   severe psychiatric disorders |
| Interventions | 11a | Not applicable. The study is to analyse the potential of new media for documentation. This can be considered as observational study. |
|  | 11b | Criteria for discontinuing are death, leaving Ulm or acquiring of exclusion criteria. |
|  | 11c | NEMO provides a user friendly interface for elderly individuals (clear design, big fonts, and auditory feedback) helping an easy fill in of questionnaires. |
|  | 11d | There are no interventions that are permitted or prohibited during the trial. |
| Outcomes | 12 | Primary Outcome:  Patient acceptance of a new medium of communication  Change of occurred adverse events  Secondary Outcome:  Maintenance of chemotherapy doses through better adverse event management  Change in the quality of life |
| Participant timeline | 13 | Both parts of the study are planned to last 6 months and build on each other (see Fig 1 and Table 4). |
| Sample size | 14 | Sample size was determined with the statistical software G*Power (v3.1.9.4) We assumed an effect size of 1, corresponding to a side effect variation of 1 on the Likert scale, a type I error rate = 0.05, and a power of 80%. Planning for a Mann-Whitney test comparing the difference between two groups led to a required sample size of 18 individuals per group (Fig 2). |
| Recruitment | 15 | The first part will be used to assed the right group of subjected that later on will allow random assignment in the second part of the study. |
| **Methods: Assignment of interventions (for controlled trials)** | | |
| Allocation: |  |  |
| Sequence generation | 16a | The physician's desktop application belonging to the app provides the pseudonym NEMO-Identifier for the participating test person. This is an isolated system that is independent of the smartphone app. |
| Allocation concealment mechanism | 16b | Method of random allocation of patient will be set in at the time of the beginning of the study. |

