| Statistical methods | 20a | Wilcoxon-Mann-Whitney test will be used to assess known-groups validity, as well as to compare differences between NEMO users and patients with standard reporting procedure concerning the severity of occurred adverse events. NEMO uses a Likert scale to score each questionnaire item. To rate the overall effect of adverse event management, a summary score will be calculated from a weighted sum of questionnaire items by the maximum number of items. Spearman correlation will be used to evaluate convergent validity between each item and the summary score of the quality of life questionnaire or its symptom scales. The impact of the side effect management will be analyzed by comparing changes in an item's scoring between the reevaluation steps during tumor therapy. This comparison will be made using a Jonckheere-Terpstra test |
|  | 20b | All statistical details have been given. |
|  | 20c | We set up in NEMO reminders for the patients in order to minimize potential missing data points. |
| **Methods: Monitoring** | | |
| Data monitoring | 21a | Members of the protocol committee and biometry and statistical analysis will be in charge of monitoring the pseudonymised data. Statical approach for analysis is described above in section 20a-c. |
|  | 21b | For exclusion we refer to 10c. Interim data will be accessed by the committee described in 21a. Study leaders and coordinator will be in charge of deciding for study termination. |
| Harms | 22 | Not applicable to the trial. The aim of the trial is to assess new media communication for report and reduction of adverse events. |
| Auditing | 23 | Not applicable to the trial. |
| Ethics and dissemination | | |
| Research ethics approval | 24 | Consent was obtained in a written form by the ethics committee Ulm University, Ulm, Germany - Proposal no. 406/19. |
| Protocol amendments | 25 | All relevant involved parties will be informed of important protocol modifications. |
| Consent or assent | 26a | All patients will have to sign a written declaration of consent in order to participate to the study. All participants will be informed of procedure and endpoint. They will be also given the possibility to ask questions to coordinators before consenting to take part to the study. Also, possibility of withdrawing consent at any time is an option. |
|  | 26b | This point is not applicable to the study. No biological specimens will be taken. |

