| Confidentiality | 27 | Patients data will be passed to clinicians in offline modality and through QR code. |
| Declaration of interests | 28 | No competing interests for principal investigators is declared. |
| Access to data | 29 | In the study phase, the desktop application, which stores all master data of the test persons on a computer that is protected against access, is the data storage. In a later phase, a login system for the desktop application will be set up. It is planned to integrate the application into the hospital's clinical information system to ensure legally compliant documentation and data protection of personal data according to the applicable standards. Technical staff of the project will only receive data in pseudonymized form. Thus, it is not possible for these employees to draw conclusions about individual persons.  For the evaluation of the study, the data is transferred to the Trusted Third Party, pseudonymized and released for analysis. Additionally, the Trusted Third Party checks the plausibility of the data (monitoring). |
| Ancillary and post-trial care | 30 | The study has an observatory nature. No drugs or treatments will be provided, and therefore potential harm to participants is not possible. |
| Dissemination policy | 31a | After evaluation of the data, a prompt and speedy publication of the results is planned. There will be a publication to answer the main question (regardless of the results). |
|  | 31b | As authors are involved: The study committee as well as the principal investigators of the study center, who contributed significantly to the recruitment by including more than 10% of the total number of study participants. Additional authors will be included for evaluation or manuscript preparation according to their scientific input. |
|  | 31c | Study protocol is planned to be published under open access. |
| Appendices |  |  |
| Informed consent materials | 32 | Figure 1: Trial design  Figure 2: Sample size estimation  Table 1: Smartphone questionnaire chemotherapy  Table 2: Smartphone questionnaire immunotherapy  Table 3: Feasibility questionnaire  Table 4: Flow chart of study procedure |
| Biological specimens | 33 | No biological specimens will be used in the trial. |

Figure 1: Trial design

Figure 2: Sample size estimation

Table 1: Smartphone questionnaire chemotherapy

Table 2: Smartphone questionnaire immunotherapy

Table 3: Feasibility questionnaire

Table 4: Flow chart of study procedure

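### The protocol declares harm impossible and the study observational, yet app entries inform therapy in both parts and part 2 randomises patients to the app.

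*Protocol*

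**What the plan says.** Four statements set the harm position.

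- Item 30 (Ancillary and post-trial care): "The study has an observatory nature". It adds that no drugs or treatments are supplied and concludes that "potential harm to participants is not possible".
- Item 22 (Harms): "Not applicable to the trial. The aim of the trial is to assess new media communication for report and reduction of adverse events".
- Item 11a (Interventions): "This can be considered as observational study".
- Item 17a: patients and physicians know the allocation.

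Other items describe what is done.

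- Item 8 (Trial design): app data are "transmitted securely via QR-codes to the treating physician and used for future therapy settings". This sentence comes before the text separates the two parts.
- Item 8, part 2: "36 participants will be randomly assigned a group of 18 persons". App users log daily and their data are transferred every second month. Controls report what they remember at appointments.
- Item 7 (Objectives): "Reduction of side effects by at least 1 degree according to CTCAE at study start".
- Item 12 (Outcomes): change in adverse events is a primary outcome, and maintaining the chemotherapy dose is a secondary one.
- Items 19 and 27: the app is offline, and data pass to clinicians by QR code.
- Items 20a, 21a and 21b: adverse event severity is compared between arms, a committee sees interim data, and the study leaders and coordinator may terminate the study.

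**The concern.** Supplying no drug does not make a changed decision about an existing drug harmless. The participants are on combination chemotherapy or at least two checkpoint inhibitors (item 10). If a reporting route is expected to alter toxicity and preserve dose, it can in principle move either in the wrong direction. Toxicity may be under-reported or misread, a full dose may be kept when it should have been reduced, or a logged symptom may be seen late. These examples are inference, not statements in the protocol. What the protocol does is rule such events out in advance.

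At stake is whether an event that followed a therapy decision made on app data, or a delay because a symptom sat unread in the app, would be recognised and recorded as such. Items 22 and 30 give staff a written reason not to look.

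**Working it through.** This is mainly a consistency check, with some arithmetic for scale.

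**1. Is the study observational?** Items 11a and 30 say so. Item 8 assigns 36 patients at random to app or standard care. Allocation by the study to a reporting route, with outcomes expected to differ because of it, is an interventional comparison. The label is wrong for part 2. Part 1 is non-randomised, but its patients also use the app.

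**2. Does item 30's inference hold?** The premise is that the study provides no treatment. The conclusion is that harm is impossible. The step fails because item 8 feeds app data into decisions about treatment that patients already receive.

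**3. Is there a concrete route in the text?** The app is offline (item 19) and data pass by QR code (items 19 and 27). In part 2 the transfer is every second month. Over 6 months that is 6 / 2 = 3 transfers, so an entry can wait up to about two months before anyone at the clinic reads it through the app.

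**4. Who is exposed?** All 30 patients in part 1 and 18 in part 2 use the app: 30 + 18 = 48 users, at most 48 × 6 = 288 patient-months. Part 2 alone gives 18 × 6 = 108.

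**5. What does the planned comparison cover?** Inputs from item 14: effect size 1, type I error 0.05, power 80%, Mann-Whitney test, 18 per group. Two-sided testing and normal data are assumptions, since item 14 states neither sidedness nor distribution. The Mann-Whitney test is approximated by a t-test with n scaled by 3/π:

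- Effective n = 18 × 3/π = 17.2 per group. The noncentrality is d × √(17.2 / 2) = 2.93 for d = 1.
- The smallest n reaching 80% is 18, with power 0.81, so the stated figure reproduces. A one-sided test would need 14.
- For a worsening of d = 0.5, the noncentrality is 1.47 and power is 0.30 (simulation 0.28).

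**6. What could clean data show?** If no app-attributed event occurred, the one-sided 95% upper limit is 1 − 0.05^(1/n). For n = 18 this is 15.3%; for n = 48 it is 6.1%.

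The figures in steps 5 and 6 hold for any study of these sizes. They do not measure the effect of items 22 or 30, and the fix does not change them. They show only that the data could not establish impossibility.

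**The case against.** The strongest reply is that toxicity is already at the centre of the plan. Change in adverse events is a primary outcome, physicians derive CTCAE scores, severity is compared between arms, and doses are recorded: "Physicians will additionally fill out an electronic case report form containing tumor stage and information about therapeutic substances and doses". A committee sees interim data, the study can be stopped, and item 31a commits to publication whatever the results. All of this stands. A reader might infer that a report following items 22 and 30 would show the study as harm-free by definition. The documents do not support that, because adverse events by arm would be reported. What is missing is narrower: handling an event as a harm and linking it to the app or to a decision based on it.

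Three further points stand in part.

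- The protocol speaks of maintaining dose, not of altering it. Item 8 nevertheless compares applied doses and uses app data for therapy settings.
- Daily logging detects more than recall at appointments. A raw comparison of severe events by arm could make the app look harmful through better detection alone, so the planned comparison is not a clean safety signal in either direction.
- A reader might infer that patients are never told to report severe symptoms directly. That cannot be asserted. The consent pages and the study flow chart (Table 4) are not available, and item 26a says participants are informed of the procedure. App users also attend for therapy and can speak to staff; nothing says that oral reporting stops.

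**Conclusion.** The statements in items 22 and 30 and the observational label are wrong as written, and the contradiction lies within the protocol itself, so it is not a matter left to a statistical analysis plan. It is not confined to part 2: the use of app data for therapy applies to all 48 app users, while the interventional label concerns the randomised 36. No estimate, test or sample size changes.

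The size of the risk cannot be derived from the document and may be low. It would be wrong to infer that the app is unsafe or that toxicity goes unrecorded. The conclusion rests on the text of items 8, 19 and 27, and on the judgement that a route able to improve toxicity management could also worsen it. The correction is worth making because it is cheap and bears on safety.

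**What to change.** 1. In item 30, delete the claim that harm cannot occur. In items 11a and 30, describe part 2 as a randomised interventional comparison.
2. In item 22, replace the current entry with a short harms entry on the existing eCRF, for app users in both parts and for controls in part 2. Record physician-documented unplanned admissions and CTCAE grade 3 or higher events. Report them descriptively, by arm in part 2, with the caveat that daily logging detects more than recall at visits.
3. Add one free-text field for any event that the treating physician attributes to the app or to a decision based on its entries.
4. Unless the consent material already says so, state in the protocol that app entries are read only at QR transfer and that severe symptoms must be reported directly to the clinic.

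The cost is some protocol wording and a few eCRF fields. Grade 3 or higher events can largely come from the CTCAE scoring already planned. Randomisation, endpoints and sample size stay as they are. The drawback is that attribution is unblinded, so it can only be descriptive.
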